## Methods

### Design

The trial will take place in government-funded secondary schools in the Western Sydney region of Australia, one of the fastest growing areas in the nation. This region has a large proportion of youth who come from low socio-economic status (SES) and immigrant backgrounds [43, 44], meaning they are at greater risk of physical inactivity compared with the Australian average [45].

This will be a two-arm, cluster randomized controlled trial with allocation at the school level (1:1 ratio to intervention and control conditions). See CONSORT flow diagram (Fig. 2). School years in Australia run from the end of January to the middle of December, with a summer break from mid-December to late January. Assessments will be completed at baseline of the first year (Term 1, February-April) and post-intervention (Term 4, September-December 2014: 7–8 months after baseline), which is the primary endpoint for this trial. A maintenance phase assessment will be conducted 14–15 months after baseline (Term 2, May–July).

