### Sample size

Sample size calculations were based on estimated effect sizes for the primary outcome. A recent meta-analysis [3], indicated that lesson planning and delivery interventions have a pooled effect of *d* = 0.60 on MVPA during PE lessons. To ensure 80 % power to detect an effect of this size would require 90 participants in a non-clustered trial (two-tailed probability level of 0.05). We considered the clustered nature of the data, including both school and class levels [46]. However, results from recent studies of MVPA in PE lessons indicated that clustering at the school level was negligible after accounting from clustering at the class level [22, 33]. As a result, we adjusted our sample size calculations for clustering using the formula 1 + (*m*-1)ρ, where *m* is the number of students per class and ρ is the intra-class correlation (ICC) [46].

Our recent study in Sydney-area schools indicated a class-level ICC of 0.62 [22], which was similar to Aelterman et al. [33] who reported a class-level ICC of 0.63. With an estimated class size of 22 participating students, an adjustment of 14.23 was required: 1 + (22–1)*0.63 = 14.23. Multiplying by the 90 participants required in non-clustered trial, we estimated that 1280 students would need to participate to achieve 80 % power. We estimate that 14 schools, with a mean of 4.5 classes of Year 8 students per school can be recruited and, therefore, aim to recruit 1386 students (14 schools × 4.5 classes per school × 22 students per class). Potential loss to follow up of up to 30 % of participants (*n* = 384; a very conservative estimate) will not substantially impact on the statistical power of the study. This resilience to loss of power exists because this study will use generalized mixed models, enabling the inclusion of all participants (included at baseline) in the analyses. In non-clustered longitudinal clinical trials, this analytic approach has been shown to yield similar point estimates and smaller decreases in statistical power than multiple imputations [47, 48].

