### Recruitment and randomization

Principals and Head Teachers of PE from all secondary schools that meet our eligibility criteria will be invited to express their interest in participating in this study. From the schools that indicate an interest in the study, we will attempt to purposively select schools in order to ensure that the sample is representative of the region’s population, in terms of school size and gender composition (i.e., single sex or co-educational). Schools that agree to participate will be match paired according to SES of the postcode in which the school is located (according to the Index of Relative Socio-Economic Disadvantage:), school size (Year 8 enrolment), gender composition of PE classes (i.e., single sex vs co-ed) and the duration of PE lessons. Using a computer-based randomization plan generator, the 14 schools will be randomized to the control or intervention condition from within each pair following baseline assessments. A researcher not associated with recruitment or data collection, and who will be blind to school identity, will carry out randomization procedures.

All PE teachers in schools that enter the trial will be invited to an information session during which study procedures will be outlined and questions answered. The research team will present study information and provide an information letter and consent form to all Year 8 students from classes whose teacher agrees to participate.

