### Statistical analysis

Between-arm differences in changes on the primary and secondary outcomes will be analyzed using generalized linear mixed models according to intention-to-treat and per-protocol principles. Specifically, intention to treat analyses will involve analysis of outcomes collected from all students who completed baseline assessment, regardless of whether or not they complete post-intervention or maintenance phase assessments. Between-arm differences in changes on the primary and secondary outcomes will be assessed by including an indicator variable for group allocation (arm), a variable representing time (baseline, post-intervention, and/or maintenance) and their interaction.

For the primary outcome (MVPA during lessons), student data will be gathered from between one and three lessons per student at each of the time points (baseline, post-intervention and maintenance). The repeated measure will be modeled as a random intercept effect. Lesson will also be modeled as a random intercept effect. Analyses will also be adjusted for class and teacher clustering-each teacher will be given a case ID. In instances where teachers ‘team-taught’ (i.e., two teachers within a single lesson), we will create a new case ID that is unique to that combination of teachers. In some instances students will be taught by different teachers within a time point (i.e., from lesson to lesson) or across time points (e.g., from baseline to post-intervention). We will account for this data structure by specifying cross-classified random effects models. Possible school-level residual clustering will be explored and included in the models, if appropriate. In sum, we will include four random intercept effects: (i) lesson; (ii) student; (iii) teacher; and (iv) class. We will consider a fifth random intercept effect for school, if preliminary analyses suggest clustering of MVPA during lessons at the school level.

We will also control for a number of variables that could influence students’ MVPA during lessons. These include temperature at the start time of the lesson, the type of activity included in the lesson and the timing of accelerometer fitting for the lesson (the student arrived at lesson wearing an accelerometer or was fitted at started of lesson).

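### Schools are randomised, but the primary model includes a school effect only if a preliminary look suggests clustering, so arm x time can be tested as if classes had been randomised

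*Protocol article*

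**What the plan says.** The Design section describes a "cluster randomized controlled trial with allocation at the school level (1:1 ratio to intervention and control conditions". Under Recruitment and randomization, "the 14 schools will be randomized to the control or intervention condition from within each pair following baseline assessments".

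The Statistical analysis section assesses between-arm differences in change through the arm x time interaction. For the primary outcome it commits to four random intercepts: lesson, student, teacher (cross-classified) and class. School is treated differently: "Possible school-level residual clustering will be explored and included in the models, if appropriate", and again, "We will consider a fifth random intercept effect for school, if preliminary analyses suggest clustering of MVPA during lessons at the school level". The section does not say what would count as suggesting clustering, or which data the preliminary analyses use.

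The Sample size section adjusts for class-level clustering only. Its reason is that two earlier studies of MVPA in PE found negligible school clustering once class was allowed for. It gives no school-level ICC.

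**The concern.** In a cluster trial the evidence for an arm effect comes from variation between randomised units. There are 14 of them here, which gives at most 12 error degrees of freedom for the arm comparison, or 6 if the matched pairs are kept in the analysis. If school is left out, the comparison rests on variation between classes, with about 61 degrees of freedom (63 - 2).

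The plan lets the data decide which of the two applies. A preliminary look at 14 schools will often miss a school component large enough to matter, so finding none is weak reassurance. At stake is whether the primary test keeps its stated level. This is a stated rule for the primary model that makes the randomised unit optional, so it is more than a detail left to a later document.

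**Working it through.** **1. The plan's own figures reproduce.** The Sample size section states that "lesson planning and delivery interventions have a pooled effect of" d = 0.60, with 80% "power to detect an effect of this size would require 90 participants in a non-clustered trial" at a "two-tailed probability level of 0.05". A two-sample t-test needs 45 per arm, so 90 in total. The ICC comes from the study "who reported a class-level ICC of 0.63".
- Design effect: 1 + (22 - 1) x 0.63 = 14.23.
- Students needed: 90 x 14.23 = 1280.7 (stated as 1280).
- Recruitment target: 14 x 4.5 x 22 = 1386 students, in 14 x 4.5 = 63 classes.

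**2. Assumed input.** Let rho_s be the correlation between students in the same school but different classes. The protocol gives no value, so it is varied here, with the total same-class correlation held at 0.63.

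**3. Power of a preliminary look.** In simulated class means at one time point (14 schools, 63 classes), an F-test for school at 5% detects rho_s = 0.02 in 9% of trials, 0.05 in 19% and 0.10 in 40%. The 5% level is an assumption.

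**4. The planned contrast is a change.** A school effect that is the same at both time points cancels from post minus baseline. Let f be the share of school variance that is time-specific, and assume that half of the class variance is stable. For class-mean changes:
- school variance of change: 2 x f x rho_s
- class variance of change: 2 x [0.5 x (0.63 - rho_s) + 0.37/22]
- ICC of change: school variance / (school + class variance)
- variance inflation when school is ignored: 1 + (4.5 - 1) x ICC of change
- type I error: 2 x [1 - Phi(1.96 / sqrt(inflation))]

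| rho_s | f | School variance | Class variance | ICC of change | Inflation | Type I error (formula) | Type I error (simulated) |
|---|---|---|---|---|---|---|---|
| 0.05 or 0.10 | 0 | 0 | - | 0 | 1.00 | 5.0% | about 5.0% |
| 0.05 | 0.25 | 0.025 | 0.614 | 0.039 | 1.137 | 6.6% | 6.5% |
| 0.05 | 0.50 | 0.050 | 0.614 | 0.075 | 1.264 | 8.1% | 8.0% |
| 0.10 | 0.25 | 0.050 | 0.564 | 0.081 | 1.285 | 8.4% | 8.6% |
| 0.10 | 0.50 | 0.100 | 0.564 | 0.151 | 1.527 | 11.3% | 11.3% |

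**5. The conditional rule as a whole.** With school tested at 5% first, and a school-level test used only when it is detected, simulated type I error for the same range of f is about 6% to 7% at rho_s = 0.05 and 7% to 8% at 0.10. Always testing at school level on 12 df holds about 5%.

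**6. What honest accounting costs.** The design effect with school is 1 + 21 x 0.63 + (4.5 - 1) x 22 x rho_s = 14.23 + 77 x rho_s. At rho_s = 0.05 this is 18.08. With 1386 students, d = 0.60 and a t-test on 12 df, power is 0.78, 0.73, 0.68 and 0.59 at rho_s = 0, 0.02, 0.05 and 0.10. The class-only calculation gives 0.84. These are single-time-point figures, as in the protocol's own calculation.

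**The case against.** The strongest reply is that the plan tests a change, so a stable school effect drops out. That is correct. A reader who simulates one time point would find type I error of about 8% and 12% at school ICC 0.05 and 0.10 with school left out, and might carry those figures over to the primary test. They do not carry over unless school effects shift between assessments. The protocol gives some reason to think they could: group mentoring is run school by school, with staff working out how to support each other's implementation.

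Second, the protocol has grounds to expect little school clustering, from two earlier studies. This stands as a rationale. However, no estimate is given, and the finding concerns MVPA in lessons, whereas the same modelling approach serves the secondary outcomes.

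Third, the 5% pre-test is assumed. With a 20% pre-test, in the single-time-point simulation, the rule stays at about 4.8% to 5.8% for school ICC from 0.02 to 0.20. This also stands, but the protocol sets no such threshold.

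Fourth, teachers belong to schools, so the teacher effect may absorb some school variation. The simulation has no teacher effect, so this could reduce the inflation.

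A reader might also infer that the choice is made on unblinded outcome data. The text does not say so. Randomisation follows baseline assessment, and clustering can be estimated without arm labels.

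**Conclusion.** The concern holds in conditional form. The plan makes the randomised unit an optional term with no stated criterion, and 14 schools give a preliminary look little power to find clustering that matters.

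The documents do not support a flat statement that standard errors are too small or that type I error exceeds 5%. With school effects that are zero or constant over time, the arm x time test keeps its level. Inflation needs school effects that vary over time. If a quarter to a half of the school variance is time-specific, type I error is about 6.5% to 8% (school ICC 0.05) or 8.5% to 11% (0.10) when school is omitted, and about 6% to 7% or 7% to 8% under a 5% pre-test.

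These sizes rest on an assumed school ICC, an assumed time-specific share, half of the class variance being stable, and a simplified simulation without teacher effects.

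**What to change.** In the Statistical analysis section, delete both conditional statements about school. State instead that:
- school is always in the model, whatever its estimated size, as a random intercept **and** a school-by-time random effect. The intercept alone is not enough, because it largely cancels from a change contrast;
- arm x time is tested with a small-sample correction based on the 14 schools, for example Kenward-Roger or Satterthwaite, with at most 12 df;
- the same applies to primary and secondary outcomes.

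This changes analysis wording only; recruitment and data collection are unaffected. The price is somewhat wider confidence intervals and lower nominal power than the class-only calculation implies.

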#### Hypotheses

We hypothesize that, compared with students in the control condition, students whose teacher participates in the intervention will be:Be more active during PE lessons (i.e., greater proportion of lesson time spent in MVPA, as well as moderate PA and vigorous PA measured separately).Spend a lower proportion of PE lessons being sedentary.Report greater needs satisfaction in PE, as well as higher autonomous motivation and lower controlled motivation and amotivation towards PE and leisure-time MVPA.Accumulate more MVPA and less sedentary time during leisure time (i.e., outside of school).More engaged in academic lessons that follow PE lessons.Report greater physical self-concept and subjective well-being.

We also hypothesize that intervention effects:7.On MVPA and sedentary behavior during PE lessons will be mediated by changes in student autonomous motivation and psychological needs satisfaction as well as teacher behavior that provides opportunities for students to engage in MVPA.8.On MVPA behavior during leisure time will be mediated by changes in autonomous motivation towards leisure-time MVPA.9.On student engagement in academic lessons will be mediated changes in MVPA they accumulated during the preceding PE lesson.10. On physical self-concept and subjective well-being will be mediated by changes in overall levels of MVPA accumulated.

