Maximising Movement and Skill Development	1. Include an active warm-up with dynamic stretching.
	2. Provide lots of equipment.
	3. Employ circuits and rotations.
	4. Use grids effectively.
	5. Implement small sided games.
	6. Organise non-elimination games.
	7. Modify games to maximize activity and skill development.
	8. Integrate fitness into activities.
	9. Choose activities that maximize MVPA.
Reducing Transition Time	1. Manage the change room effectively.
	2. Take the roll while students are active.
	3. Early activity set-up.
	4. Distribute equipment quickly.
	5. Decrease talk/instructions.
	6. Form groups efficiently.
	7. Manage water breaks efficiently.
Building Competence	1. Provide overview of lesson/unit.
	2. Make behavioural expectations clear.
	3. Use questioning.
	4. Provide effective positive feedback.
	5. Provide effective corrective feedback.
	6. Match task to ability level.
	7. Limit peer comparison.
	8. Promote self-comparison.
Supporting Students (including support for students’ autonomy and relatedness needs)	1. Emphasise fun and variety.
	2. Circulate around the class.
	3. Provide students with opportunities to make choices.
	4. Provide a rationale and emphasise relevance.
	5. Minimise controlling language and behavior.
	6. Take the students’ perspective.

Definitions for each principle and strategy can be found in Additional file 1.

Importantly, many aspects of the face-to-face workshop will be delivered using web-based resources. For example, best/poor practice videos will be accessed through the project website during face-to-face workshops. Teachers will also conduct their first self-reflection task during the workshop by accessing videos of their lessons that will be uploaded onto the project website. Teacher self-reflection will involve a rating of their implementation of each AMPED strategy (1 to 5 stars) and free-text response explaining why they provided this rating. See an example in Fig. 3. Additional file 1: Appendix B provides details of all ratings and descriptions. Thus, for much of the workshop, teachers will work independently on the web platform, but project staff will be available to provide assistance at any stage.

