#### Primary outcome

MVPA during PE lessons-ActiGraph accelerometers (ActiGraph, LLC, Fort Walton Beach, FL) will be used to measure PA during three PE lessons at each time point (baseline, post-intervention, and maintenance). Accelerometer models will include GT1M, GT3X, and GT3X+, which have been shown to have extremely high levels of agreement both in terms of counts per minute and MVPA estimates [50]. Accelerometers will be attached using cotton, elastic belts to the students’ hip at the top of the right iliac crest.

Lesson start and end times will be signified by the school bell and will be recorded by researchers on site. These times will be used to process accelerometer data and determine PA that occurs during each PE lesson.

Prior to data collection, accelerometers will be initialized and set to record data using a 1 sec epoch or 60hz (for GT3X+). Data will be processed using Actilife software (Version 6, ActiGraph, LLC, Fort Walton Beach, FL), with 1 sec vertical axis data used to classify activity intensity according to Evenson and colleagues’ [51] cutpoints, which have been shown to be the most accurate in this age group [52]: moderate-to-vigorous activity >2296 counts per minute. To convert the cutpoint definition for 1 s epochs, the cut-point will be divide by 60.

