#### Covariates-related to MVPA during PE lessons

Temperature at the start of the PE lesson will be measured using an electronic thermometer (HC520 Thermometer, CS Raffles Tech Inc., Singapore). The type of activity being taught during the lesson will also be recorded and categorized as follows: (i) invasion games; (ii) striking and fielding games; (iii) target games; (iv) net/wall games; (v) fitness activities; (vi) artistic activities; (vii) athletics; (viii) other; and (ix) mix of activities. Finally, at some lessons students will arrive wearing an accelerometer that they have been provided in order to measure their daily MVPA (7-day wear period). For other lessons, students will be fitted with an accelerometer when they arrive at the lesson. The timing of this fitting (i.e., do they arrive at the lesson wearing an accelerometer or not?) will be recorded for each student at each lesson.

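### The lesson-MVPA model controls for activity type recorded after randomisation, which a taught strategy can change, so the arm-by-time term may not estimate the total effect

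*Protocol article*

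**What the plan says.** The Statistical analysis section sets out the random effects for the primary outcome and then adds covariates without any condition: "We will also control for a number of variables that could influence students’ MVPA during lessons". The list is start-of-lesson temperature, then "the type of activity included in the lesson and the timing of accelerometer fitting for the lesson".

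The section on covariates explains the second item: "The type of activity being taught during the lesson will also be recorded and categorized as follows". Nine categories follow. Most are game or sport families, such as invasion games and net/wall games. They also include fitness activities, a mix of activities, and other.

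The Primary outcome section has MVPA measured "during three PE lessons at each time point (baseline, post-intervention, and maintenance"). Schools are "randomized to the control or intervention condition from within each pair following baseline assessments" (Recruitment and randomization).

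Table 2 lists what teachers are trained to do. Under the principle on maximising movement, strategy 9 is "Choose activities that maximize MVPA" and strategy 8 is "Integrate fitness into activities".

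The first research question asks, without qualification, what the intervention does to lesson MVPA. The article describes no primary analysis without activity type, no restriction to its baseline values and no sensitivity analysis that omits it.

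**The concern.** A covariate that is fixed before allocation, or that allocation cannot touch, can be adjusted for without changing what the treatment term means. Activity type at follow-up is neither. It is observed after schools are randomised and teachers trained, and one taught strategy is about which activities to choose.

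Holding it fixed turns the arm-by-time term into a comparison of lessons of the same type. If trained teachers move towards more active kinds of lesson, that is a success of the programme, yet the adjusted estimate does not count it. The result would then answer a narrower question than the first research question. Conditioning on such a variable can also distort what remains if activity choice and MVPA share unmeasured causes, for instance the facilities available.

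The other two covariates do not share the problem. Training does not affect temperature, and whether a student arrives already wearing the device follows from the measurement schedule.

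**Working it through.** **1. Order of events.** Baseline lessons come first, then randomisation, then training in Terms 2 and 3, then post-intervention lessons in Term 4, then maintenance lessons the following year. Activity type is recorded lesson by lesson, so only its baseline values precede allocation.

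**2. Which strategies can move the covariate.** Table 2 has 9 + 7 + 8 + 6 = 30 strategies. Strategy 9 concerns the choice of activity itself. Strategy 8 could arguably turn a games lesson into one coded as fitness or as a mix. The others need not change the recorded category.

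**3. The plan's own figure.** Inputs from the Sample size section: d = 0.60, two-sided 0.05, 80% power, 22 students per class, ICC 0.63.
- The t-based two-sample formula gives 44.6, so 45 per arm and 90 in total.
- Design effect: 1 + (22 − 1) × 0.63 = 14.23.
- 90 × 14.23 = 1280.7, against 1280 stated. Recruitment target: 14 × 4.5 × 22 = 1386.

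The sample size reproduces and is not in dispute.

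**4. Share of the effect removed.** Let p be the extra proportion of lessons that training moves into a more active category, and g the MVPA difference between categories in SD units. The part running through activity type is p × g, and its share of the planned effect is p × g / 0.60. The document gives neither p nor g; these values are assumptions.

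| p | g = 0.3 | g = 0.6 | g = 0.9 |
|---|---|---|---|
| 0 | 0% | 0% | 0% |
| 0.10 | 5% | 10% | 15% |
| 0.20 | 10% | 20% | 30% |
| 0.30 | 15% | 30% | 45% |

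**5. Check of direction.** A simulation used p = 0.20, g = 0.6 and a within-category effect of 0.48, so the total is 0.48 + 0.20 × 0.6 = 0.60. The arm-by-time coefficient was 0.606 without activity type and 0.484 with it: 1 − 0.484/0.606 = 20% removed, as in the table. This was a plain regression without clustering; it checks the mechanism and does not predict the trial's result.

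**6. What a given loss would mean for power.** With effective n per arm = N / (2 × 14.23), power is about Φ(d√(n/2) − 1.96). For N = 1280, n = 44.98; at d = 0.60 this is Φ(0.60 × 4.742 − 1.96) = Φ(0.885) = 81.2%.

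| Assumed share removed | d left | N = 1280 | N = 1386 |
|---|---|---|---|
| 0 | 0.60 | 81.2% | 84.2% |
| 10% | 0.54 | 72.6% | 76.0% |
| 20% | 0.48 | 62.4% | 65.9% |
| 30% | 0.42 | 51.3% | 54.5% |

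These rows hold residual variance fixed. Adjustment may reduce it, which would offset some of the loss shown.

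**The case against.** The best defence is that adjustment serves a purpose. With 14 schools and one to three lessons per student at each time point, the arms could differ by chance in the sports being taught when researchers visit, and sport plausibly affects MVPA. The categories are also coarse, so training may hardly move lessons between them. Strategy 9 may mean picking more active drills within a scheduled unit; its definition is in an additional file that is not shown.

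Much of this stands. It makes the size of the bias uncertain and allows it to be near zero. It does not justify conditioning the primary estimate on something the training may change. The article gives no such rationale beyond saying that these variables could influence MVPA, and it does not say that the curriculum fixes what is taught.

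Three stronger readings are tempting and not supported:
- A reader might infer that circuits and small-sided games also move the covariate. They need not: a small-sided invasion game is still an invasion game, and circuits can be run within a unit.
- A reader might infer that the authors themselves treat activity type as a mediator, because hypothesis 7 refers to "teacher behavior that provides opportunities for students to engage in MVPA". That hypothesis does not name activity type. The article lists activity type among covariates and measures teachers' use of the strategies separately, from video ratings.
- A reader might infer that a large part of the effect is bound to be lost. No figure in the document supports that.

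**Conclusion.** The point holds in conditional form. The article commits the lesson-MVPA model to a covariate whose follow-up values arise after randomisation and which at least one taught strategy, arguably two, can change. If lessons move between categories because of training, the arm-by-time term omits that part of the effect and no longer answers the first research question. The likely direction is towards no effect, since the strategy aims at more active lessons.

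The amount is unknown. The 5% to 45% range for non-zero shifts rests wholly on assumed shifts of 10 to 30 percentage points and category differences of 0.3 to 0.9 SD. With no shift there is no loss by this route. Changes within a category, which most of the 30 strategies would produce, remain in the estimate. The conclusion rests on what the article states; a full analysis plan is not shown.

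**What to change.** Delete activity type from the covariates of the primary model, and from the models for sedentary, light, moderate and vigorous time in lessons wherever the same covariates are carried over. Keep temperature and timing of accelerometer fitting. Report the activity-adjusted model beside the primary result, labelled as a sensitivity or mechanism analysis that estimates the effect with activity type held fixed. A table of activity types by arm and time point would let readers see whether lessons moved between categories.

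Adjusting for each class's baseline mix of activities instead is unnecessary. Nine categories from about three lessons per class would be sparse, and students have moved to Year 9 by the maintenance phase.

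The change takes one sentence and no new data. Its price is possibly a somewhat larger lesson-level residual variance, and no correction in the primary estimate for chance imbalance in the activities taught; the sensitivity analysis would show how much that matters.

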Generalized linear mixed models will be also used to examine mediation hypotheses. Mediating effects will be estimated using a cluster-bootstrapped based product-of-coefficients test that is appropriate for cluster randomized controlled trials [75].

Potential moderators of the intervention effects will also be explored. Potential moderators will include gender and ethnic background (categorical variables), as well as socio-economic status and baseline levels of physical activity and psychosocial variables (e.g., motivation and needs satisfaction) which will be treated as continuous variables. Moderator effects will be explored using the same generalized mixed modeling approach by including appropriate interaction terms in the regression models. The trial is powered to detect main effects, not interactions; thus, we will employ a less stringent significance level to explore potential moderators. Interaction terms that are significant at *p* < 0.1 will be explored by testing differences in intervention effects across sub-groups stratified according to the moderator variable [76].

Per protocol analyses will investigate the influence of teachers’ adoption of the intervention, as indicated by the proportion of intervention components completed by each teacher (e.g., workshops attended and online tasks completed), on student outcomes (e.g., MVPA during PE lessons). Analyses will also examine the effect of teachers’ implementation of the intervention, as indicated by increases in their use of AMPED teaching strategies from baseline to post-intervention (observed in video recordings of their lessons), on student outcomes.

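### With 14 randomised schools, a cluster bootstrap of the mediated effect can reject too often unless the arm-to-mediator path carries small-sample uncertainty

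*Protocol article*

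**What the plan says.** The mediation plan is two sentences in the protocol's Statistical analysis section: "Generalized linear mixed models will be also used to examine mediation hypotheses", followed by "Mediating effects will be estimated using a cluster-bootstrapped based product-of-coefficients test that is appropriate for cluster randomized controlled trials", with a citation. The section does not name the resampled unit, the interval type, any small-sample correction or a significance level for mediation.

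Under Recruitment and randomization, schools are matched in pairs and "the 14 schools will be randomized to the control or intervention condition from within each pair following baseline assessments". The Design section gives a 1:1 ratio, so there are 7 schools per arm in 7 pairs.

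The Sample size section adjusts for class only, because in earlier studies of MVPA in PE lessons "clustering at the school level was negligible after accounting from clustering at the class level". The Statistical analysis section adds a school effect only if preliminary analyses show that lesson MVPA clusters by school.

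**The concern.** The arm-to-mediator path compares randomised schools, so its uncertainty comes from 14 units however many students are measured. A bootstrap that resamples 7 schools per arm understates the variance of that contrast and uses near-normal tail quantiles where a t distribution is needed. Resampling classes gives more units, but treats classes in one school as independent.

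If the second path is well estimated, the error of the product is close to the error of the first path. An intervention that does not move motivation or needs satisfaction could then be reported as working through them more often than the nominal level implies. Research question 3 and Hypotheses 7 to 10 rest on this test. The Background faults earlier interventions for not examining theoretical mediators, so these results will carry weight. The primary outcome analysis is not involved.

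**Working it through.** **The plan's own figures.** The protocol gives no error rate for the mediation test, so there is none to reproduce. Its sample size does reproduce. A two-sample t-test with d = 0.60, two-sided 0.05 and 80% power needs 44.6, so 45 per arm and 90 in all. With "an adjustment of 14.23 was required: 1 + (22–1)*0.63 = 14.23", 90 × 14.23 = 1280.7, against the stated 1280. The planned structure is 14 × 4.5 = 63 classes and 63 × 22 = 1386 students.

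**Closed form, first path, 7 v 7 schools resampled within arm (percentile interval, matching ignored).**
- The bootstrap variance is (k − 1)/k of the unbiased estimate. With k = 7, √(6/7) = 0.926.
- The effective critical value is 1.96 × 0.926 = 1.815. The value needed is t(12) = 2.179.
- The width ratio is 1.815/2.179 = 0.83.
- The two-sided error is P(|t12| > 1.815) = 9.5%.
- If the 7 pairs are resampled instead, P(|t6| > 1.815) = 12.0%.

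**Simulation of the product.** The set-up was 14 schools, 63 classes, 22 students per class, least-squares paths, a 95% percentile interval, 1,000 resamples and 2,000 trials per setting (Monte Carlo standard error about 0.7 points near 10%). From the protocol come the school, class and student numbers and the class ICC of 0.63 for the outcome. Assumed are the sizes of path a (arm to mediator) and path b (mediator to outcome), school ICCs of 0 or 0.1 for mediator and outcome, and a mediator class ICC of 0.2 (0.1 when the school ICC is 0.1). Error in %:

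| School ICC | True paths | Schools, within arm | Schools, unstratified | Classes, within arm |
|---|---|---|---|---|
| 0 | a = 0, b = 0.5 | 9.7 | 9.0 | 5.9 |
| 0 | a = 0, b = 0.2 | 10.1 | 8.0 | 5.7 |
| 0 | a = 0.6, b = 0 | 9.8 | 8.6 | 7.2 |
| 0 | a = 0.3, b = 0 | 6.6 | 5.8 | 3.2 |
| 0 | a = b = 0 | 0.8 | 0.3 | 0.2 |
| 0.1 | a = 0, b = 0.5 | 9.7 | 8.9 | 26.2 |
| 0.1 | a = 0, b = 0.2 | 9.2 | 8.6 | 23.6 |
| 0.1 | a = 0.6, b = 0 | 8.2 | 5.8 | 9.3 |
| 0.1 | a = 0.3, b = 0 | 3.2 | 2.5 | 5.2 |
| 0.1 | a = b = 0 | 1.0 | 0.4 | 1.6 |

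**Smaller school ICCs, classes resampled, a = 0.** The error was 6.6% at a mediator school ICC of 0, 12.8% at 0.02 and 18.8% at 0.05.

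**Strength of the second path, schools resampled, a = 0.** The error was 0.3% when path b's true z is 0, about 1% at 1, about 4% at 2 and about 8% at 3. It reached 9–10% from z = 4.

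**Pair matching, schools resampled within arm, a = 0.** In one set-up the error was 8.9%, 7.7%, 5.9% and 4.5% at assumed within-pair correlations of 0.1, 0.2, 0.3 and 0.4. In another it was 6.9% at 0.3 and 5.3% at 0.6. The sizes differ, but the error falls as matching works better in both.

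**Alternative.** A Monte Carlo product interval with the first path drawn from t(12) gave 5.1–5.4% under a null first path.

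**The case against.** A reader might infer that the planned test has a true error of 9–10%, at any school ICC, with intervals always about 17% too narrow. The documents do not support that, for four reasons.

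- **The test is not fully specified.** The resampled unit, interval type and level are inferred. The 0.05 level appears only in the sample size calculation. A journal article commonly leaves bootstrap detail to the analysis plan, and the cited method source is not shown, so a correction may exist.
- **The null for a product is composite.** The 9–10% figure is close to the worst case. A weak second path brings the error well below it. For teacher behaviour, one of the mediators in Hypothesis 7, the second path rests on teachers or about 63 classes, so its precision cannot be assumed.
- **Schools are matched.** Resampling within arm ignores the pairs, so effective matching offsets some or all of the shortfall.
- **Class resampling is near nominal on the protocol's own assumption.** The 13–19% figures need school ICCs that the protocol does not give.

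All four stand as limits on size. They do not remove the point, which is not about missing detail. The protocol asserts that the method suits this design, yet neither natural resampling unit reliably holds 5% when the intervention leaves the mediator unmoved. That null is the relevant one, because the Background already cites associations between motivation and activity. The statement on school clustering cannot justify class resampling in general: it concerns lesson MVPA, which is the mediator only in Hypothesis 9, and says nothing about motivation or needs satisfaction.

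**Conclusion.** The concern holds in a conditional form: with 7 schools per arm, an uncorrected cluster bootstrap can be anti-conservative for the mediation hypotheses. The school-resampling figure of about 8–10% needs all of the following: a percentile interval, a nominal 5% level, a null first path, a clearly non-zero second path and little gain from matching. The class-resampling figures depend on the mediator's school ICC, which the documents do not give. Whether the trial would meet the unfavourable conditions cannot be told from the protocol. This is a worthwhile, inexpensive improvement to a non-primary analysis, not a threat to the trial's main conclusion.

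**What to change.** In the mediation paragraph of the Statistical analysis section, name the school as the independent unit and carry small-sample uncertainty in the arm-to-mediator path. Either of two methods would do this:

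- a Monte Carlo (distribution-of-the-product) interval with the first path drawn from a t distribution on school-level degrees of freedom; or
- a joint-significance test with that t reference for the first path.

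The degrees of freedom are 14 − 2 = 12, or 7 − 1 = 6 if the pairs are modelled. Keep the cluster bootstrap, resampling whole schools, as a sensitivity analysis, and state the level used for mediation.

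The cost is a few sentences and a few lines of code. Mediation intervals become up to about 20% wider (1/0.83 = 1.20), with some loss of power for mediation. A bootstrap with a small-sample correction might also serve, but would need its error rate checked at 7 schools per arm. The primary outcome analysis does not change.
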